### Study population

The study population will be farmers, traders, women of reproductive age and children between 2 and 5 years of age in the Ho West district.

### Sample size calculation

Sample size was calculated using STATA software, accounting for a 30% (25) anticipated improvement in nutrition and reduction in waste due to the intervention. A total of 140 households (70 per group) were determined to be sufficient, assuming 80% power, a 5% significance level, and 10% non-response.

Separate sample size calculations were done for farmers and market vendors using a single proportion in STATA 14. The total sample size for these groups was set at 70, incorporating a 10% non-response rate. The estimated proportion of postharvest loss was 20%, confidence level was 0.95%, level of significance was 0.05.

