## Research design and methods

### Study setting

The study will be conducted in the Ho West District of the Volta Region in Ghana. The Ho West district shares borders with the Republic of Togo, and its capital, Dzolo-Kpuita, is located 175 km northeast of Accra. The total population is 95,000 (20). Anaemia and undernutrition remain critical public health issues in this region. Recent national trends indicate that anaemia prevalence among children under 5 years, although decreasing, remains alarmingly high at 48.9% as of 2022, down from 76.1% in 2003 (21). In the Volta Region specifically, hospital-based data shows that over 55% of children under five are anaemic (22). Stunting, a marker of chronic undernutrition, also affects nearly one in five children under five in Ghana (23). In the Ho West district, 73.5% of the people work in agriculture in some capacity. Less than 1 % (0.06%) of households involved in agriculture are involved in fish farming, with the majority (95.2%) in crop farming (47). Farmers in this region cultivate a diverse range of fruits and vegetables, including bananas, pineapples, mangoes, pears, and oranges. These four farming communities, Abutia Kissiflui, Dededo, Amedzofe, and Kpedze, will be the focus of the study. The district’s busiest market, located in Abutia Kissiflui, generates up to 75% of the district’s tax revenue. Contributions from Dededo, Amedzofe, and Kpedze are 12.3, 8.7, and 4%, respectively. Kpedze has a population of 4,692 people, of which 12% are children under the age of five and 51% are women. There are 3,360 people living in Dededo, 16% of whom are children under five, and 53.3% of whom are women. A total of 1,561 people reside in Amedzofe, with 51.2% of them being women and children. With 1,667 residents, Abutia Kissiflui has a female population of 54% and a child population of 13.5% (20, 24). The district’s southernmost neighbourhoods, Kpedze and Amedzofe, were selected for the intervention group, while the northernmost neighbourhoods, Dededo and Abutia Kissiflui, were designated as the control group. Out of the 14 towns in the district, these towns were specifically chosen. To prevent contamination, the control and intervention groups were selected based on their proximity to one another and their geographic location. Also, data on nutritional treatments and services provided in each group will be recorded.

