### Randomisation and allocation procedure

Cluster randomisation will be employed to ensure baseline comparability between the intervention and control groups for key characteristics, including age, weight, and known risk factors. The four selected farming communities will be stratified by geographic location (north and south of the district). Within each stratum, one community will be randomly allocated to the intervention group and one to the control group. Randomisation will be performed by an independent researcher using a computer-generated random number sequence. Allocation will be concealed from the field research team to reduce the risk of selection bias. Due to the nature of the intervention, blinding participants will not be feasible, as the differences between intervention and control conditions are easily observable. However, to minimise bias, the researcher responsible for delivering the intervention will be different from the researcher responsible for allocating clusters. Additionally, outcome data will be collected by individuals blinded to group assignment (44).

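### The 80% power claimed for 140 households is not supported for a trial that allocates four communities, and the 140 cannot be reproduced from the inputs given.

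*Protocol article*

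**What the plan says.** The section on sample size calculation in the protocol article bases the household sample on one effect, "accounting for a 30% (25) anticipated improvement in nutrition and reduction in waste due to the intervention", and concludes: "A total of 140 households (70 per group) were determined to be sufficient, assuming 80% power, a 5% significance level, and 10% non-response". These are all the inputs printed for the household comparison. The 20% loss figure in the same section belongs to the separate single-proportion calculation for farmers and traders.

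The section on randomisation and allocation makes the community the unit of allocation: "The four selected farming communities will be stratified by geographic location", and one community in each of the two strata goes to each arm. The statistical analysis section names a t-test for comparisons within and between groups and mentions no term for community.

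**The concern.** Households in one community share markets, harvests, health services and the group sessions themselves, so their outcomes are likely to be correlated. A power figure for a trial that allocates communities has to allow for that correlation and for the number of communities. The printed inputs allow for neither.

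A reader who wants to check the 140 is also stopped at the effect size. One 30% is attached to two different things, nutrition and waste, with nothing to say what it is 30% of.

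At stake is how the result will be read. With a stated power of 80%, a null finding looks like adequately powered evidence that the education programme does not work.

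**Working it through.** **Inputs from the protocol article.** 70 households per arm, power 80%, significance level 5%, non-response 10%, four communities with two per arm. Hence 70 × 0.9 = 63 evaluable households per arm and 63/2 = 31.5 per community.

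**Assumptions, because the article gives no value.** Two-sided test; ICC of 0, 0.01, 0.02 or 0.05; effect of 0.5 SD, or 50% versus 20%.

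**Step 1: can 70 per arm be reproduced?**

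- *30 percentage points.* The requirement is largest at 65% versus 35%: 42.4, so 43 per arm, or 48 after dividing by 0.9. With continuity correction it is 49, or 55 after loss. No baseline gives 70.
- *30% relative reduction.* 70 per arm appears only at baselines of about 0.78–0.79 without continuity correction, or 0.81–0.82 with it.
- *30% relative increase.* 70 per arm appears only at baselines of about 0.68 (without) or 0.70 (with).
- *0.3 SD.* 175 per arm, or 195 after loss.
- *0.5 SD.* n = 2 × (1.960 + 0.842)² / 0.5² = 62.8, so 63 per arm, and 63/0.9 = 70. This is an exact match, but it assumes independent households and an effect size that the article does not state.

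The printed inputs therefore neither yield 140 nor rule it out.

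**Step 2: power with two communities per arm, effect 0.5 SD.** In SD units, the standard error of the difference between arms is SE = √[ICC + (1 − ICC)/31.5]. Large-sample power is Φ(0.5/SE − 1.96). Community-level power uses the noncentral t distribution with 4 − 2 = 2 degrees of freedom, noncentrality 0.5/SE and critical value 4.303. The 95% CI half-width is 4.303 × SE.

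| ICC (assumed) | SE | 0.5/SE | Large-sample power | Power on 2 df | Half-width (SD) |
|---|---|---|---|---|---|
| 0 | 0.178 | 2.81 | 80% | 35% | ±0.77 |
| 0.01 | 0.204 | 2.46 | 69% | 29% | ±0.88 |
| 0.02 | 0.226 | 2.21 | 60% | 25% | ±0.97 |
| 0.05 | 0.283 | 1.77 | 42% | 18% | ±1.22 |

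Larger communities do not solve this. As households per community increase, SE² falls only to the ICC, while 80% large-sample power for 0.5 SD needs SE² of about 2/63 = 0.032. From an ICC of about 0.032 upwards, no number of households in two communities per arm reaches 80%.

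**Step 3: the reading most favourable to the plan, 30 percentage points (50% versus 20%).** SE = √{[(0.5 × 0.5 + 0.2 × 0.8)/63] × (1 + 30.5 × ICC)}.

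| ICC (assumed) | SE | 0.30/SE | Large-sample power | Power on 2 df |
|---|---|---|---|---|
| 0 | 0.081 | 3.72 | 96% | 52% |
| 0.01 | 0.092 | 3.26 | 90% | 43% |
| 0.02 | 0.102 | 2.93 | 83% | 38% |
| 0.05 | 0.128 | 2.34 | 65% | 27% |

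On this reading large-sample power stays above 80% up to an ICC of about 0.02, but a large-sample approximation is not reliable with four communities.

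**The case against.** The strongest reply has four parts.

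*The 140 has not been shown to be wrong.* This stands. A reader might infer that 140 contradicts the 30%. The article does not support that, because a relative change gives 70 per arm at some unstated baselines, and the baseline may sit in a full protocol or in the cited source, neither of which is shown. The supportable statement is that 140 cannot be reproduced from what is printed.

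*The effect sizes and ICCs here are not the plan's.* This also stands. The 0.5 SD is inferred from the match in step 1. It is tempting to take the anaemia figures in the study setting section as the baseline, such as the regional statement that "over 55% of children under five are anaemic". Ignoring clustering, 63 per arm would then give about 46% power for a 30% relative cut from 55%, and 39% from the national 48.9%. But these are background rates in young children, not declared inputs, and anaemia is only one of several outcomes labelled primary. They do not show what power the plan intended.

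*The test on 2 degrees of freedom is not the planned test.* True: the article plans a t-test with no community term. That does not rescue the 80%. For 0.5 SD at an ICC of 0.05, an unadjusted test would reject in about 70% of trials, but with a type I error of about 22% instead of 5%. Baseline adjustment, which the tables omit, could raise power. Analysing the strata as pairs would leave 1 degree of freedom and about 17% power at ICC 0.

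*Recruitment is complete, so nothing can change.* The sample cannot, but the claim made for it can.

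The study setting, sampling and randomisation sections disagree on how communities were assigned and which lie north or south. Every version has two communities per arm, so the result is unaffected.

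**Conclusion.** The concern holds in two parts. First, the 80% is stated for 140 households with no allowance for clustering, while the trial allocates four communities; it is not supported for this design. Second, the 140 cannot be verified, because the 30% lacks an endpoint, a baseline or SD, and a statement of whether it is absolute or relative.

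The first part rests only on the article's text. Its size is conditional on the assumed effects and ICCs: a community-level comparison has 18–35% power for 0.5 SD and 27–52% for 50% versus 20% over ICCs of 0 to 0.05, so neither example reaches 80% even with no clustering at all. A reader might go further and conclude that the trial could not detect its stated effect. The article does not support that, since the stated effect is undefined.

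**What to change.** Keep the 140 households and rewrite the household paragraph of the sample size section so that it:

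1. names the endpoint, gives its baseline proportion or SD, and says whether the 30% is relative or absolute;
2. keeps the 80% only as a record of a calculation for individually randomised households without clustering, and withdraws it as the power of this trial;
3. reports, for the effect then stated, the power over a stated ICC range with two communities per arm, and the expected 95% CI half-width from a community-level comparison (for 0.5 SD planning on 2 degrees of freedom, about ±0.77 SD at ICC 0 to ±1.22 SD at ICC 0.05);
4. says that a null result cannot be read as evidence of no effect.

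The cost is rewording and a short calculation, with no extra participants or visits. The drawback is that the stated power becomes less favourable.

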### Recruitment of participants

The objective of the study will be explained to farmers, traders, and women within various households in the communities. Those who give their consent will qualify to participate in the study. The recruitment of participants will last for 1 month. To ensure adequate enrolment, the study will use community engagement through local leaders and health workers, public sensitisation via meetings and local radio, and clear communication in local languages. A multistage sampling method will ensure fair representation, while flexible scheduling and follow-up reminders will help reduce non-response and support retention.

### Inclusion and exclusion criteria

The criteria for inclusion in this study will be fruits and vegetable farmers and traders in the Ho West District.

Farmers and traders who do not deal in fruits and vegetables will be excluded, as will those who deal in fruits and vegetables outside the Ho West district. Additionally, women of reproductive age and children aged 2–5 years residing in the district will be included in the study.

Children with congenital disorders, disabilities and diseases (Malaria, HIV, TB, cancer, severe diarrhoea, etc.) and/or requiring specialised care and hospitalisation will be excluded from the study. Children with severe malnutrition (WHZ < - −3sd or HAZ < −3sd) with complications that require inpatient care, tube-fed children, and children outside the preferred age range will also be excluded. Also, Pregnant women and women with diseases such as Tuberculosis, malaria, HIV, etc., will be excluded (Figure 2).

**Figure 2 fig2:**
[figure not shown]
CONSORT flow chart of the study. Adapted from Moher et al. (50).

## Data collection

### Qualitative strand

Focus group discussions will be conducted using an interview guide developed using questions on waste and losses of fruits and vegetables at the farm, market and households, as well as factors that influence these losses. Each interview will be tape-recorded and is expected to last between 60 and 90 min.

Focus group discussions will be facilitated by a trained interviewer and assisted by a note-taker. The facilitator will lead the groups for discussions. Each focus group discussion (FGD) will last approximately 90 min. Interviews will be tape-recorded, and detailed notes will also be taken. The focus group discussion will comprise 10 farmers, traders, and women, each from the control and intervention groups.

### Quantitative strand

#### Sociodemographic characteristics

Research assistants will collect data on the socio-demographics of participants, including age, sex, level of education, occupation, income, and marital status.

#### Baseline assessment

Data will be collected using semi-structured questionnaires, a widely applied method for exploring household-level food storage and nutritional behaviours in community-based research (26, 27). The availability of fruits and vegetables, as well as their storage conditions, will be systematically observed during household visits. A structured questionnaire will be administered to gather information on sociodemographic characteristics, the quantity of fruits and vegetables purchased, consumed, stored, and the extent of food losses encountered, approaches consistent with established value-chain assessment protocols (28). Based on the quantities of reported losses, the loss estimates will be calculated using the Food Loss and Waste Value Calculator developed by Quantis as part of the WBCSD’s FReSH program (29).

## Nutritional outcomes assessment

### Anthropometric measurements

Anthropometric data—including height, weight, and Body Mass Index (BMI) for women, and z-scores for children—will be collected using standardised procedures as outlined by recent World Health Organisation guidelines (9, 42). Duplicate measurements will be recorded for each participant to ensure accuracy, and the average of the two will be used for analysis. Adult participants who can stand unassisted will be weighed barefoot and wearing minimal clothing using a calibrated Seca 876 digital scale. For infants and children unable to stand, measurements will be taken using a Seca 354 baby scale, with children either naked or in a clean, dry diaper. BMI will be computed as weight (kg) divided by height squared (m^2^) and categorised based on WHO classification thresholds. Z-scores (weight-for-height, weight-for-age, and height-for-age) will be generated using the WHO Anthro software to assess the nutritional status of children.

### Dietary diversity score

A 24-h dietary recall will be conducted to assess food intake. Participants will report all food and beverages consumed in the 24 h before the interview (41). Foods will be classified under ten categories based on FAO dietary diversity guidelines (30, 31):

Roots and tubersCereals and grainsNuts and seedsMeat, poultry, and fishEggsDairyDark leafy vegetablesVitamin A-rich fruitsOther fruitsOther vegetables

Minimum dietary diversity will be defined as consumption of at least five out of ten food groups for women, and four out of seven for children, per WHO/FAO guidelines (9, 32). If a food group is consumed, a score of 1 will be given; otherwise, a score of 0.

A fruit and vegetable frequency questionnaire will also be used to assess the frequency of consumption of different fruits and vegetables. This structured questionnaire will be interviewer-administered and developed based on locally available produce. Women will report the frequency of fruit and vegetable consumption as: more than once daily, once a week but not daily, once a month but not weekly, or rarely/never. The same approach will be used for their children.

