## Introduction

Post-harvest loss (PHL) is defined by the Food and Agriculture Organisation (FAO) as the measurable reduction in both the edible mass (quantity) and nutritional value (quality) of food intended for human consumption (1). The post-harvest system includes several interconnected processes that begin at harvest and extend through processing, marketing, preparation, and ultimately, household consumption. At each of these stages, substantial food losses occur globally, resulting in decreased food availability and accessibility (2, 40).

Globally, an estimated one-third (1.3 billion tonnes) of food produced for human consumption is lost or wasted annually (1). These losses are particularly severe in developing countries, where they can lead to income reductions of at least 15% for an estimated 470 million smallholder farmers and others along the food value chain (3, 4). Most of these losses are attributed to food loss along the value chain, which accounts for approximately 90% of total waste (5). This has far-reaching implications for food prices, food security, and nutritional health (38).

In Sub-Saharan Africa and other low-income regions, plant-based foods form the key source of household diets, supplying nearly 90% of daily energy and 80% of protein requirements (5). However, these food categories, including grains, fruits, vegetables, legumes, and tubers, represent up to 92% of all post-harvest losses in the region. Among them, fruits and vegetables experience the highest losses, with estimates suggesting that nearly 45% are discarded or wasted before reaching consumers (6, 7).

Post-harvest loss of fruits and vegetables is a significant concern for achieving food security and reducing global hunger (8, 9). In Ghana, approximately 30–50% of fruits and vegetables are lost along the entire value chain (10–12). These losses occur at different stages, including harvesting, handling, storage, and retail. A study in Ethiopia showed that post-harvest handling, storage, and marketing account for 85.6, 11.6, and 2.8% of total losses, respectively (46, 48). As a result, there is a decreased availability of essential, nutrient-rich foods, especially for vulnerable groups such as women and children, who have high nutritional needs (13). The shift towards less nutritious, processed, or starchy foods due to limited access to fresh produce further worsens micronutrient deficiencies (14, 15).

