### Food consumption score

The food consumption score (FCS) will be determined by asking participants to recall all food and beverage consumption in the 7 days before the interview. Food groups will include: main staples, pulses, meat/fish, fruits, vegetables, milk, oil, and sugar. Consumption frequencies will be summed within each group and multiplied by group-specific weights. The weighted scores will be summed to derive the total FCS. FCS categories will be:

0–21: poor21.5–35: borderline35: acceptable

A score below 35 will be interpreted as indicative of household food insecurity.

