### Secondary outcome

The secondary outcomes will be to evaluate the fruit and vegetable intake of women and children, post-harvest practices among farmers, traders, and women, food waste behaviour of women, BMI-for-age in women and children, the knowledge level of women regarding fruits and vegetables, and the impact of these on nutritional outcomes (Table 2).

**Table 2 tab2:** Table of primary and secondary outcomes.

Outcome type	Outcome	Measurement method	Assessment time points
Primary	Anaemia status in women and children	Haemoglobin testing (Hemocue 501 meter)	Baseline and post-intervention
Primary	Dietary Diversity Score (DDS)	24-h dietary recall and food group classification	Baseline and post-intervention
Secondary	Household food waste behaviour	Structured food waste behaviour questionnaire	Baseline and post-intervention
Secondary	Fruit and vegetable intake	Food Frequency Questionnaire (FFQ)	Baseline and post-intervention
Primary	Post-harvest handling knowledge/practices	Survey and Focus Group Discussion	Baseline
Primary	Anthropometric measurements (BMI, z-scores)	Height, weight using WHO protocol	Baseline and post-intervention

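### The Dietary Diversity Score, a primary outcome, has no category for pulses, and its only printed classification has ten groups while children are judged on four of seven

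*Protocol article*

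**What the plan says.** Protocol article, Dietary diversity score section: a 24-hour recall captures everything eaten and drunk, and "Foods will be classified under ten categories based on FAO dietary diversity guidelines". The list that follows has two starchy groups (roots/tubers and cereals/grains), nuts/seeds, flesh foods (meat, poultry and fish together), eggs, dairy, two vegetable groups (dark leafy and other) and two fruit groups (vitamin A-rich and other). The scoring rule is "If a food group is consumed, a score of 1 will be given; otherwise, a score of 0". Minimum diversity is then "consumption of at least five out of ten food groups for women, and four out of seven for children", with a reference to WHO/FAO guidelines.

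Table 2 marks the score as primary, assessed at baseline and post-intervention.

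The next section, Food consumption score, defines a second diet measure from a 7-day recall: "Food groups will include: main staples, pulses, meat/fish, fruits, vegetables, milk, oil, and sugar". There pulses are a group of their own and staples are one group.

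The Introduction, writing of Sub-Saharan Africa and other low-income regions, describes plant foods as the key source of household diets and names the categories concerned, "including grains, fruits, vegetables, legumes, and tubers".

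**The concern.** Two printed rules do not work as they stand.

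- **Pulses.** Under the 0/1 rule a food earns a point only through a listed category. Pulses have none. They score nothing, or someone places them in another category, such as nuts/seeds, by a decision the protocol does not state.
- **Children.** The single classification has ten groups, but the child criterion has a denominator of seven. The text gives no seven-group list and no rule for collapsing ten into seven. Several collapses are possible, and the text does not choose among them.

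A related question is whether roots/tubers and cereals/grains should be two groups in the women's score. It matters because it moves scores the opposite way from the missing pulses group.

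At stake is a primary outcome. Two analysts following the protocol could report different scores, and different proportions reaching minimum diversity, from the same recalls.

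**Working it through.** **1. Count of the list.** Starchy 2 + nuts/seeds 1 + flesh foods 1 + eggs 1 + dairy 1 + vegetables 2 + fruits 2 = 10, as stated. Groups for pulses: 0. Seven-group lists: 0.

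**2. Example diets for a woman (cut-off 5).** The comparison scoring merges the two starchy groups and adds pulses, which keeps the total at ten. It is used only to show sensitivity; it is not taken from the cited guideline.

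| Diet | As printed | Starches merged, pulses added |
|---|---|---|
| Cereal, beans, leafy vegetable, fish, other fruit | 4, fails | 5, passes |
| Cereal, tuber, leafy vegetable, other vegetable, fish | 5, passes | 4, fails |
| Cereal, tuber, beans, leafy vegetable, fish | 4, fails | 4, fails |

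The first diet turns on pulses alone: it contains one starch, so merging changes nothing. The second passes only because two starches count separately. In the third the two features cancel.

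**3. Children: 4 of 7 against 4 of 10.** The documents give no consumption frequencies. Assume each group is eaten independently with probability p. Then P(at least 4 of n) = Σ C(n,j) p^j (1−p)^(n−j), summed over j = 4 to n. At p = 0.5:

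- n = 7: (35 + 21 + 7 + 1)/128 = 64/128 = 0.500
- n = 10: 1 − (1 + 10 + 45 + 120)/1024 = 848/1024 = 0.828

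| p | 4 of 7 | 4 of 10 | Difference |
|---|---|---|---|
| 0.2 | 0.033 | 0.121 | 0.088 |
| 0.3 | 0.126 | 0.350 | 0.224 |
| 0.4 | 0.290 | 0.618 | 0.328 |
| 0.5 | 0.500 | 0.828 | 0.328 |
| 0.6 | 0.710 | 0.945 | 0.235 |

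**4. Women: net effect on the proportion reaching 5 of 10.** Assumed and independent: roots r = 0.5 or 0.8, cereals c = 0.5 or 0.9, pulses u = 0.1, 0.3 or 0.6, and each of the other eight groups q = 0.3 or 0.4. Let K be the number of those eight eaten, binomial (8, q).

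- Passes only as printed: both starches, no pulses, K = 3. Probability r·c·(1−u)·P(K=3). Largest: 0.8 × 0.9 × 0.9 × 0.2787 = 0.181. Smallest: 0.5 × 0.5 × 0.4 × 0.2541 = 0.025.
- Passes only under the comparison scoring: pulses eaten, with exactly one starch and K = 3, or no starch and K = 4. Probability u·[P(one starch)·P(K=3) + P(no starch)·P(K=4)]. Largest: 0.6 × (0.5 × 0.2787 + 0.25 × 0.2322) = 0.118. Smallest: 0.1 × (0.26 × 0.2541 + 0.02 × 0.1361) = 0.007.

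Over the grid, printed minus comparison prevalence runs from 0.418 − 0.508 = −0.090 to 0.602 − 0.429 = +0.173, or about −9 to +17 percentage points.

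**5. Women: mean score.** For one woman, printed minus comparison score is +1 if she eats both starches, −1 if she eats pulses, and 0 if both or neither apply. The expected difference is r·c − u, from 0.25 − 0.6 = −0.35 to 0.72 − 0.1 = +0.62 groups on the same inputs.

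**The case against.** The strongest reply has five parts.

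- **For women the plan is internally consistent.** Ten groups are scored and the cut-off is five of ten. A reader might infer that separate roots and cereals groups depart from the guideline. That cannot be established without the guideline's own list, which is not at hand, so the split is a question to settle and not a shown error.
- **The Food Consumption Score is a different instrument.** It uses a 7-day recall with weighted frequencies, and its groups need not match; it also has one fruit group and one vegetable group where the diversity list has two of each. This stands. The comparison shows only that the protocol itself treats pulses as a distinct part of the diet to be measured. Likewise, the Introduction does not call legumes a staple of Ho West diets.
- **The child mapping is detail commonly left to a manual or analysis plan.** This would hold had the article been silent. It prints one classification and a cut-off with another denominator, and the two do not correspond. The reply is right that the text does not say 4 will be applied to ten groups; the 22 to 33 points are conditional on that reading.
- **The t-tests concern means, not the cut-off.** The cut-off matters only for the yes/no indicator. But the mean score also depends on whether pulses count, as step 5 shows.
- **The trial contrast is not shown to be biased.** A reader might infer that women and children are misclassified in both arms, or that the comparison is distorted. The documents do not support either. Nothing suggests that scoring differs by arm or visit, children's status is undefined and not shown to be wrong, and for women the two features offset each other to an unknown degree.

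**Conclusion.** The point holds in a limited form. As printed, the score gives pulses no credit, and the child criterion does not match the score it is meant to be applied to. Both follow from the text alone.

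The sizes are illustrations. Applying 4 to ten groups instead of seven adds about 22 to 33 percentage points to a child's chance of passing for p from 0.3 to 0.5, and less at p = 0.2. For women, individual diets change status in both directions, and the net change of about −9 to +17 points has no established sign. All these figures rest on assumed, independent consumption probabilities.

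The consequence is a primary outcome that is not fixed for children and is at risk of misclassification for women. It warrants an amendment before analysis.

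**What to change.** Amend the Dietary diversity score section before analysis:

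1. Make pulses a scored group. Added as a separate group to the present list this gives 10 + 1 = 11, so the women's groups must be settled as a set.
2. Reconcile the women's ten groups with the guideline the protocol cites for the five-of-ten cut-off, including whether roots/tubers and cereals/grains are one group or two.
3. Print a separate seven-group list for children with a food-to-group mapping, and apply four of seven only to that list.
4. Rescore baseline and post-intervention recalls by the same rules in both arms.

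The cost is one amended section and desk recoding. The 24-hour recall already records all foods, so no new data are needed provided the food-level records are kept. The Study status and timeline section says no results had been analysed at submission, so at that stage the mapping could still be fixed without knowledge of the results.
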